## Abstract

**Introduction:**

Poor adherence to photoprotection for people with xeroderma pigmentosum (XP) can be life-threatening. A randomised controlled trial (RCT) is being conducted to test the efficacy of a personalised adherence intervention (XPAND) to reduce the level of ultraviolet radiation (UVR) reaching the face, by improving photoprotection activities in adults with XP.

**Methods and analysis:**

A two-armed parallel groups RCT, where we randomised 24 patients with suboptimal adherence to either an intervention group who received XPAND in 2018 or a delayed intervention group who will receive XPAND in 2019. XPAND involves seven sessions, one-to-one with a facilitator, using behaviour change techniques and specially designed materials to target barriers to photoprotection. Following baseline assessment in April 2018 (t0) and intervention, the primary outcome will be measured across 21 consecutive days in June and July 2018 (t1). The primary outcome is the average daily UVR dose to the face (D-to-F), calculated by combining objective UVR exposure at the wrist (measured by a dosimeter) with face photoprotection activities recorded on a daily UVR protection diary. Secondary outcomes include average daily UVR D-to-F across 21 days in August (t2); psychosocial process variables measured by daily questions (t0, t1, t2) and self-report questionnaires (t0, t1, t2, December 2018 (t3)). Intervention cost-utility is assessed by service use and personal cost questionnaires (t0, t3). The delayed intervention control arm participants will complete three further assessments in April 2019 (t4) and June–July 2019 (t5), and December 2019 (t6) with dosimetry and UVR protection diary completed for 21 days at t4 and t5. A process evaluation will be conducted using mixed methods.

**Ethics and dissemination:**

Ethical approval has been received from West London & GTAC REC 17/LO/2110. Results will be disseminated in peer-reviewed journals and at conferences. This study tests a novel intervention, which, if successful, will be integrated into routine care.

**Trial registration number:**

NCT03445052; Pre-results.

Strengths and limitations of this studyTo the best of our knowledge, this is the first randomised controlled trial to evaluate an adherence intervention designed to improve photoprotection in people diagnosed with xeroderma pigmentosum.We have a primary outcome which is clinically relevant.We control for seasonal differences in environmental ultraviolet radiation exposure by comparing between groups across the same weeks.We include a process evaluation to understand participant views of XPAND which will be important when integrating the intervention into current clinical care.Recruitment and retention of participants may be difficult in this extremely rare disease.

## Introduction

Xeroderma pigmentosum (XP) is a very rare genetic condition, where the body is unable to repair ultraviolet radiation (UVR)-induced damage to DNA caused by daylight.^1^ Any UVR exposure dramatically increases the chances of developing skin and eye cancers (eg, rates of non-melanoma skin cancer increase 10 000-fold).^2^ Photoprotection is *recommended* for the healthy population and those taking medications which may cause photosensitivity. However, it is *essential* for people with XP. There is currently no cure for this disease and the only way to minimise and delay the cancers is meticulous and absolute photoprotection every day. Photoprotection involves a complex set of behaviours (ie, application of broad-spectrum SPF50 sunscreen, wearing long sleeves and long trousers or skirts, wide brimmed hat, glasses, face scarf or buff and avoiding UVR exposure by staying indoors). The best way of protecting the face is by wearing a face visor (a legionnaire style hat with a UVR-protective transparent film at the front). Analysis of self-reported photoprotection used by 21 adults with XP in the UK revealed that over half were using ‘very poor’ or no photoprotection for at least 20% of all outdoor time.^3^ This poor photoprotection has life-threatening consequences.

In common with other rare conditions,^4^ little is known about the psychological and behavioural patient-related factors that have the potential to improve health outcomes in patients with XP. In recognition of this deficit, the National Institute of Health Research (NIHR) agreed to fund a novel programme of research to investigate the psychosocial factors associated with non-adherence to photoprotection in XP (RP-PG-1212–20009: Developing a psychological intervention to improve ultraviolet protection and clinical outcomes in XP). The aims of the grant were twofold: to identify the drivers of non-adherence using complex mixed-methods research (qualitative interviews; cross-sectional survey; n-of-1; diary-dosimeter measures)^5^ (known as ‘Phase One’) and to use this knowledge to design and test an intervention to improve adherence (‘Phase Two’). We identified 17 modifiable psychosocial drivers of non-adherence to photoprotection activities from Phase One. These drivers or barriers to optimal photoprotection relate to factors influencing the motivation to protect (eg, doubts about perceived necessity of photoprotection) and volitional factors limiting the enactment of photoprotection activities, even if motivation is high (eg, lack of habit). Findings from the mixed-methods research studies are published separately.^3 6 7^

We aimed to systematically develop an adherence intervention to improve photoprotection in XP. There is growing support for interventions focused on changing patient beliefs about their illness and treatment, translating into improvements in adherence across a range of chronic conditions.^8–10^ This suggests that addressing unhelpful illness and treatment beliefs may be an important treatment target for photoprotection in XP. Furthermore, a recent systematic review found evidence in support of the effectiveness of psychosocial interventions to improve adherence to photoprotective activities among non-XP individuals at elevated risk for melanoma (due to personal or family history^11^).

We designed a personalised intervention titled, ‘XPAND: Enhancing XP Photoprotection Activities – New Directions’, using intervention mapping.^12^ Intervention mapping starts by breaking the desired behaviour and determinants of behaviour into constituent parts, which are mapped to theory and translated to intervention components. Relevant theories to guide the intervention design included the Necessity and Concerns Framework,^13^ Common Sense Model of Illness Regulation^14^ and the Theoretical Domains Framework (not a theory itself but it combines the components of social cognition models used to explain behaviour).^15^ A full description of the development of the intervention, the process of personalisation and the final intervention product will be reported separately.

This paper describes the protocol for a randomised controlled trial (RCT) to test the efficacy of XPAND to lower the dose of UVR reaching the face, by improving adherence to photoprotection. This can be achieved by minimising overall UVR exposure (ie, time spent outside) and by increasing level of photoprotection worn or applied when outside. The primary objective is to reduce the average daily UVR dose to the face (D-to-F) across 21 days in June to July (2018), immediately after the delivery of the main intervention. Secondary objectives are: to maintain reductions in average daily UVR D-to-F across 21 days in August 2018 (after a booster session has been delivered to the intervention group); to increase and then maintain daily ratings of mood, self-efficacy, goal priority, automaticity and photoprotection activities across the two 21-day periods. Tertiary objectives are to explore intervention-related changes from baseline. A qualitative process evaluation will investigate the acceptability, feasibility and change mechanisms from the perspective of the participant. We will conduct a cost-utility analysis, which will indicate whether implementation into clinical care is economically viable.

## Methods and analysis

### Participants and recruitment

People diagnosed with XP and registered at the National XP Service at Guy’s and St Thomas’ NHS Foundation Trust will be recruited into the trial. Eligible patients will be sent an invitation letter, followed by a telephone call from the research nurse, and those interested will be sent the study information leaflet. Following a second call, if they wish to participate, they will give written consent at a home visit. Patients will be reminded that participation in the study is voluntary and that they may withdraw at any time. No payment will be given for participation. Screening and recruitment will take place between February and March 2018.

### Inclusion criteria

A confirmed diagnosis of XP (reduced DNA repair activity in DNA fibroblast assay, in a clinical context compatible with a diagnosis of XP and with confirmation by finding pathogenic mutations in an XP gene on gene sequencing)Aged ≥16 yearsSuboptimal adherence to photoprotection when outdoors, as identified by the XP clinical team from data held in medical notes, or by the research team from data collected during the Phase One studies:Score <20 on our Adherence to Photoprotection scale (where a total score of 25 indicates optimal photoprotection)^16^Using photoprotective clothing combinations for the face that have been assessed by the clinical team as anything other than ‘excellent’ or ‘very good’ anytime outdoors,^3^ recorded on the daily UVR protection diaryHaving a ‘resistant’ or ‘integrated’ mode of adjustment to photoprotection, as identified in the qualitative analysis^7^

### Exclusion criteria

Diagnosed with cognitive impairment (XP or non-XP related) due to potential impact on the efficacy of the intervention and on the participants’ experiences of taking part.Non-fluent in English (to enable in-depth discussion with the intervention facilitators)Diagnosed with current clinical depression or anxiety, as detailed in medical notes, or confirmed after completion of Hospital Anxiety and Depression Scale (HADS)^17^ at the baseline home visit

### Study design and flowchart

The XPAND trial is a phase II two-armed parallel group RCT, with a delayed intervention control arm. Participants are randomised to either the intervention group who receive the XPAND intervention in addition to routine care between April and June 2018 or the control group who receive routine care in 2018 and then XPAND between April and June 2019. The delayed intervention control group is included to maximise information collection about the intervention due to the extremely rare nature of XP. For example, achievable sample sizes limit the ability to test between-group differences for the psychosocial outcomes with acceptable power and the delayed intervention group allows for intervention-related changes from baseline testing, which is less robust but still useful.

Patient flow through the study is described in figure 1. The baseline assessment takes place in April 2018 (t0). Post-randomisation assessments take place after completion of the intervention in June to July 2018 (t1), after a booster session in August 2018 (t2) and after a long-term follow-up in December 2018 (t3). All participants use a wrist-worn UVR dosimeter continuously from t0 to t2 and complete daily UVR protection diaries for 21 consecutive days at each assessment time point. At each assessment, participants additionally complete patient-reported outcomes. The t3 follow-up does not involve dosimetry or daily UVR protection diary. In addition, the delayed intervention control arm only completes three further assessments in April 2019 (t4) and June–July 2019 (t5), and December 2019 (t6) with dosimetry and daily UVR protection diary completed for 21 days at t4 and t5.

**Figure 1 F1:**
[figure not shown]
Progression of participants through the study.

A nested qualitative study examining acceptability and mechanisms of change will be conducted in the intervention group after the August assessment period is completed.

The study is funded by the NIHR Programme Grants for Applied Research scheme (RP-PG-1212–20009) and received ethical approval.

### Randomisation

Participants will be randomised, in blocks using an equal allocation ratio, to receive XPAND immediately (2018) or to the delayed group stratified by burning type to attempt to balance those with an extreme (ie, scoring between 1 and 3 on the sunburn severity score^18^) versus normal burning response. Participants who are in the same family will be randomised as a cluster to the same group to avoid contamination. Since all participants will be recruited at the point of randomisation, the trial statistician (SN) will generate a random allocation sequence for all participants together, using a computer programme with fixed block sizes of 4, to ensure equal allocation to both groups. To protect the integrity of the randomisation, participants in the immediate intervention group will be asked not to reveal their allocation to those outside their immediate family. Group allocation will be concealed from the XP clinical team who are not part of the research team (excluding the PI) to avoid inadvertent changes to the standard care of these participants during the trial (eg, greater/lesser discussion of adherence during routine clinical appointments). Moreover, as both the control and intervention groups might receive opportunistic encouragement from the clinical team to protect, this would not adversely affect the trial outcome.

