### Sample size calculations

The target sample size for the study is a total of 24 patients (ie, 12 per group), which was based on the ability to detect an average daily UVR D-to-F difference of 0.10 SED between the groups during the June to July 2018 assessment period. This difference was considered clinically meaningful and potentially achievable due to the personalised nature of the intervention. From our Phase One study of UVR exposure, the average daily UVR D-to-F for people diagnosed with XP was 0.27 SED (SD=0.14), with a within-person correlation of *r*
_ICC_=0.31. Thus, the anticipated difference relates to an effect size of d=0.73, or just over a one-third reduction in average daily UVR D-to-F. Adjusting for the design effect due to the dependence of assessments within individuals, a sample size of 20 patients with 21 daily observations has 80% power to detect a reduction of 0.10 SED in average daily UVR D-to-F at the 5% significance level. Accounting for attrition of 20%, based on our previous research, the target sample size was set at 24.

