### Statistical analyses

The main efficacy analyses will be conducted by the trial statistician (SN) following a prespecified analysis plan and blind to group allocation. The analysis will follow the intention to treat principle with individuals analysed within the groups to which they were randomised irrespective of whether they received or persisted with the intervention.

The treatment effect on the primary outcome of daily UVR D-to-F over 21 days between June and July 2018 and secondary outcome of daily UVR D-to-F over 21 days in August will be estimated simultaneously using a linear mixed model. Given the skewed distribution of UVR D-to-F, a logarithmic transformation will be applied and robust SE will be estimated. A random intercept will account for the repeated assessments of UVR D-to-F within individuals across all 42 days, with an autoregressive error structure to account for correlation between assessments across successive days. In addition to the dummy-coded group variable, other covariates in the model include a dummy-coded variable for the assessment period (June–July vs August), an assessment period by group interaction, the patients baseline average daily UVR, an indictor variable for the patients propensity to burn and the background level of UVR recorded by the observatory closest to the patients’ house on the day. Data will be summarised as the empirical Bayes estimate of the average daily UVR D-to-F in SEDs for each assessment period for each group.

This approach allows for missing daily data within each individual under the assumption that data are missing at random. We will run sensitivity analyses to explore the influence of missing data on the effect estimates, so as to allow for a consideration of the likely plausible range for the treatment effect under a number of missing not at random assumptions. For average daily assessments, where these are not available for the full 21 days, this will involve imputing missing values under a range of conservative assumptions using the average daily values of the group to which the individual is assigned using a pattern mixture model approach (eg, average daily level +0.0 SED to 0.5 SED).

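### Relatives are randomised together as a cluster, but the stated between-group models and the sample size allow for dependence only within individuals, so precision and power are overstated if related patients were enrolled

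*Protocol article*

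**What the plan says.** Under Randomisation, allocation is 1:1 and stratified by burning type, "using a computer programme with fixed block sizes of 4, to ensure equal allocation to both groups". Relatives are an exception to individual allocation: "Participants who are in the same family will be randomised as a cluster to the same group to avoid contamination".

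Under Statistical analyses, the primary model (June–July and August fitted together) has one random effect: "A random intercept will account for the repeated assessments of UVR D-to-F within individuals across all 42 days". Errors are autoregressive over days. The covariates are group, period, their interaction, baseline UVR, propensity to burn and same-day background UVR. Robust standard errors are planned, but the level at which they are clustered is not given. The daily secondary outcomes use the same structure. The questionnaire outcomes use linear mixed models with an unconstrained error structure and robust standard errors. Family is mentioned in none of these.

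Under Sample size calculations, the only adjustment for dependence is this: "Adjusting for the design effect due to the dependence of assessments within individuals", and on that basis "a sample size of 20 patients with 21 daily observations has 80% power".

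**The concern.** Two relatives in the trial are always in the same arm. Any similarity between them in facial UVR dose therefore adds to the variance of an arm mean, and the comparison between arms cannot cancel it. A model that treats the two as independent patients counts more information than the trial holds.

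Some similarity is plausible. Relatives may share a household, outings and habits. The stated reason for allocating them together is contamination, so the design itself expects relatives to influence one another's photoprotection. Influence of that kind arises after randomisation, so a baseline covariate cannot fully remove it.

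At stake are the width of the confidence interval and the 5% level of the primary test. With 24 patients, a few related pairs would be a sizeable share of the sample.

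**Working it through.** **Inputs from Sample size calculations**
- Target: "ability to detect an average daily UVR D-to-F difference of 0.10 SED between the groups".
- Variability: "the average daily UVR D-to-F for people diagnosed with XP was 0.27 SED (SD=0.14), with a within-person correlation of" 0.31.
- Standardised effect: "the anticipated difference relates to an effect size of d=0.73" (0.10/0.14 is 0.714, so both are used below).
- 20 evaluable patients, 10 per arm, 21 days each, 5% level. Sidedness is not printed and two-sided is assumed; a one-sided test would give 86% to 87% power, which does not match the stated 80%.

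**Step 1: reproduce the stated power.**
- Variance factor for a 21-day mean: (1 + 20 × 0.31)/21 = 7.2/21 = 0.343, square root 0.586.
- Expected z = d/0.586 × √(10/2).
- With d = 0.73: z = 2.788, and power = Φ(2.788 − 1.960) = 79.6%.
- With 0.10/0.14: z = 2.728, and power = 77.9%.

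The stated 80% is thus reached with no family term, so the calculation treats patients as independent.

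**Step 2: add families.** Let k be the number of two-member families among N analysed patients and ρ the within-family correlation of patients' 21-day means. With equal arms and relatives always together, the variance of the difference is multiplied by D = 1 + (2k/N) × ρ, however the pairs fall between arms. Then:
- true SE / naive SE = √D
- power = Φ(2.788/√D − 1.960)
- type I error of a nominal 5% test that ignores families = 2 × [1 − Φ(1.960/√D)]

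The documents give neither k nor ρ. Both are assumed, and ρ is taken before covariate adjustment.

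| Pairs among 20 | ρ | D | √D | Power, d = 0.73 | Power, 0.10/0.14 | Type I error |
|---|---|---|---|---|---|---|
| 0 | any | 1.00 | 1.000 | 79.6% | 77.9% | 5.0% |
| 1 | 0.1 | 1.01 | 1.005 | 79.2% | 77.5% | 5.1% |
| 1 | 0.7 | 1.07 | 1.034 | 76.9% | 75.1% | 5.8% |
| 2 | 0.7 | 1.14 | 1.068 | 74.2% | 72.4% | 6.6% |
| 3 | 0.5 | 1.15 | 1.072 | 73.9% | 72.0% | 6.8% |
| 5 | 0.7 | 1.35 | 1.162 | 67.0% | 65.1% | 9.2% |

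Worked row (3 pairs, ρ = 0.5): D = 1 + (6/20) × 0.5 = 1.15; 2.788/1.072 = 2.600; Φ(2.600 − 1.960) = 73.9%.

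**Step 3: all 24 patients.** Six pairs among 24 with ρ = 0.7 give D = 1 + (12/24) × 0.7 = 1.35, the same as the last row. Simulated two-sample t-tests that ignore families gave 9.5% type I error for this case. That is slightly above the formula's 9.2%, because the naive variance estimate is itself a little low when relatives are alike. One pair with ρ = 0.1 gave 5.1%.

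**Step 4: sample size.** Evaluable patients for 80% power (d = 0.73, each arm rounded up) go from 22 with no family term to between 22 and 28 over 1 to 5 pairs and ρ of 0.1 to 0.7.

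**The case against.** A reader might infer that the standard errors are too small in every analysis and that the test certainly exceeds 5%. The article does not support that, for four reasons.

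- The family rule applies only if relatives enrol, and each must separately meet the age and adherence criteria. With no multi-member family, D = 1 and there is no error. With one or two pairs the effect is modest: about 0.4 to 5.5 points of power, and type I error of about 5% to 6.5%.
- What matters is the correlation left after adjustment. Baseline UVR, same-day background UVR near the home and propensity to burn will absorb part of what relatives share. The calculations above are unadjusted and may overstate the inflation.
- Robust standard errors are planned. Clustered on family, they would address the dependence in principle. The article mentions a separate analysis plan, which is not shown and could set that level.
- The exploratory models (change from baseline including the delayed group, and the dynamic regressions) have no stated correlation structure, so nothing can be said about them here.

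All four points limit the size and reach of the concern. They do not remove the mismatch: the article prints a dependence structure that stops at the individual, and a power calculation to match, beside a randomisation rule that does not stop there. Standard errors clustered on the individual would leave correlation between relatives untouched. Background UVR measures ambient light, not shared outings or habits.

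**Conclusion.** The concern holds conditionally. The stated between-group models and the sample size do not follow the units that were randomised. Whether this distorts the result depends on two facts that the article does not give: at least one family with two or more participants, and a positive within-family correlation after covariate adjustment. If both hold and the standard errors are not clustered on family, the standard error is too small and the stated power too high.

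Over the assumed 1 to 6 pairs and ρ of 0.1 to 0.7, type I error is about 5% to 9.5%. Power at 20 patients is about 67% to 79%, against 79.6% without families (normal approximation, d = 0.73, 1 to 5 pairs). The upper end needs several families and a high correlation. An unconditional claim that inference is invalid goes beyond the documents.

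**What to change.** - **Report the number of multi-member families and their sizes.** Recruitment is complete, so this is already known. If there are none, say so and the matter is closed.
- **Make family the top-level cluster in the between-group models**, counting a patient with no enrolled relative as a family of one. Use robust standard errors clustered on family with a small-sample correction, since there are only about 20 clusters. Alternatively, use a re-randomisation test that permutes families within burning-type stratum.
- **Add a family random intercept where it can be estimated.** With a handful of pairs its variance is barely identifiable and may be estimated at zero, so it should not be the only safeguard.
- **Restate the power over a range of within-family correlations.**

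The cost is a short addition to the analysis plan, a slightly wider confidence interval and a slightly lower stated power. No new data are needed.
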